### Primary outcomes

#### Quality of life

The Pediatric Quality of Life Inventory (PedsQL 4.0) [37] is a measure of four aspects of health-related quality of life included in the subscales: Physical Functioning, Emotional Functioning, Social Functioning and School Functioning. The questionnaire will be filled out by both the parent and the sibling. Different versions are used for children aged 5–7 years and children aged 8–12 years. In this study, the Dutch version [38] of the Psychosocial Health Summary Score will be used. Specifically, the Acute version, which is filled out over the past week, will be used. The used scale has three 5-item subscales: Emotional Functioning, Social Functioning, and School Functioning. The subscale Physical Functioning is excluded, because this subscale is irrelevant for the current study. On the parent-report version and the child-report version for children aged 8–12 years, the items can be answered on a 5-point Likert scale (0 = never to 4 = almost always). On the child-report version for children aged 5–7 years, the items can be answered on a 3-point Likert scale (0 = not at all, 2 = sometimes, and 4 = a lot). An example of an item of the child-report version is: “Do you feel sad.” The internal consistency of the Psychosocial Health Summary Score was good with Cronbach’s alphas of 0.83 (child-report) and 0.86 (parent-report). Construct validity has also been demonstrated [39].

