#### Sibling adjustment to the disability of the brother or sister

The Sibling Perception Questionnaire (SPQ; originally by Carpenter & Sahler [40] and adapted by Lobato & Kao [41]) measures the impact of the disability on the sibling and the sibling’s attitude towards the disability. The questionnaire has a total of 22 items on four subscales: Interpersonal, Intrapersonal, Fear, and Communication. The Dutch version [42] of both the parent-report version and the child-report version will be used in the current study. In this study, the word “illness” in the items will be replaced by “disability.” The items can be answered on a 4-point Likert scale (1 = never to 4 = often). An example of an item is: “I feel sad about the disability of my brother/sister.” In the main data analysis, the 18-item composite Negative Adjustment Scale, which is composed of the sum of the Interpersonal, Intrapersonal and Fear subscales, will be used, because a previous study [41] found that the separate subscales have low internal consistency. The internal consistency of the Negative Adjustment Scale was found to be acceptable to good with Cronbach’s alphas of 0.79 (child-report) and 0.74 (parent-report).

In addition, parents will be asked to provide a written answer to three open-ended questions about the adjustment of the sibling to the disability of the brother or sister. The siblings will be asked to verbally answer these three open-ended questions. Their answers will be audiotaped. When there is no consent for audio recording, the researcher will type down the answers of the sibling.

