### Sample size {14}

Using GLIMMPSE 3.0 [63], the required sample size to conduct multivariate linear mixed models for the primary outcomes quality of life and sibling adjustment to the disability of the brother or sister is calculated. The sample size is estimated with an alpha of 0.05 and a target power of 0.80 and is based on an interaction effect hypothesis, including between (intervention) and within (measurement point) variance. Correlations between measurement points are estimated to be 0.60 (T0–T1; T1–T2) and 0.40 (T0–T2), based on previously found test-retest correlations on the PedsQL [64]. The correlation between the outcomes is estimated to be 0.30. This estimate is based on a previously found correlation between the SPQ and a measure of wellbeing and adjustment (Strengths and Difficulties Questionnaire; SDQ), as no information about the correlation between de SPQ and a measure of quality of life was available [65]. A scale factor of 1.2 for variability is inserted in the sample size calculation, in order to be more conservative.

For both quality of life and sibling adjustment to the disability of the brother or sister the child-report means and standard deviations from previous sibling studies are used [41, 66]. For the control group, no change is expected on the outcome measures. For the intervention group, change is expected gradually. The expected total change (at T2) on quality of life is based on the Minimal Clinically Important Difference [67]. The expected total change on sibling adjustment to the disability of the brother or sister is based on the measured change in a previous sibling intervention study [41]. No change in standard deviations is expected on all measurement points.

The computed sample size calculation based on the beforementioned parameters results in a required sample size of 134, with 67 participants in the intervention group and 67 participants in the waitlist control group. Based on two previous intervention studies [22, 29], a dropout rate of 15% is accounted for. The total required sample size is therefore 154. This includes 154 siblings and their 154 parents.

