## Statistical methods

### Statistical methods for primary and secondary outcomes {20a}

In the current study, quantitative data will be analyzed using IBM SPSS Statistics 27 [69], and qualitative data will be analyzed using ATLAS.ti. 22 [70].

The primary and secondary objectives, as well as the exploratory analysis on parenting self-efficacy, will be answered by computing the linear mixed-effects model procedure (MIXED). To test the effect of the intervention, the main effects of intervention and time, together with the interaction effect between intervention and time, will be included in the model. The primary objectives will be analyzed multivariate, whereas the secondary objectives are analyzed univariate. For the latter, the Bonferroni correction will be used to determine the alpha level. Child-report and parent-report outcomes will be analyzed separately. Cohen’s Ds will be calculated to determine the effect size. The answers to the open-ended questions will be analyzed using thematic coding with conventional qualitative content analysis [71]. The outcomes of the PAIR will be analyzed in both a quantitative way using the manual [48]. Thematic analysis of the drawings will also be executed according to the procedure described in Guidotti et al. [49]. The drawings of the PAIR are scored by two independent researchers. Intra-class correlations will be calculated to assess the inter-rater reliability.

For social validity, the mean scores will be reported. Additionally, one sample *t*-tests will be executed in order to test if the mean score significantly differs from the neutral score (3). Conventional qualitative content analysis will be used to analyze the answers to the open-ended evaluation questions [71].

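### Child-report and parent-report give two primary multivariate tests at 0.05, neither ranked nor corrected, so an either-informant reading carries about 8–10% error

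*Protocol article*

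**What the plan says.** All references are to the protocol article.

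- **Informants.** Of the PedsQL, the Quality of life section says "The questionnaire will be filled out by both the parent and the sibling". For the SPQ, the section on sibling adjustment says that the Dutch translation "of both the parent-report version and the child-report version will be used in the current study". Both instruments stand under Primary outcomes, and Table 2 lists parent and child for each.
- **Analysis.** Section {20a} says: "The primary objectives will be analyzed multivariate, whereas the secondary objectives are analyzed univariate. For the latter, the Bonferroni correction will be used". It then adds "Child-report and parent-report outcomes will be analyzed separately".
- **Alpha.** The only level given for the primary outcomes is in Sample size {14}: "The sample size is estimated with an alpha of 0.05 and a target power of 0.80 and is based on an interaction effect hypothesis".
- **Planning informant.** In the same section, for both primary outcomes, "the child-report means and standard deviations from previous sibling studies are used".

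The article does not say which informant is primary, or whether one or both must be positive for the main aim to be met.

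**The concern.** Section {20a} sets a multiplicity rule and confines it to the secondary objectives. It also splits the primary analysis by informant. Together these statements produce two primary tests of equal standing. A reader who treats a positive result on either one as success gives the trial two chances at its main conclusion, each at the planning level of 0.05.

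The two tests are not equally well founded. The sample size rests on child-report values, so the planned 80% power describes the child-report test; no power is given for parent-report. After pre-test the families know their allocation (section {17a}), and the participating parent reads the brochure and supports the worksheets. As written, a result seen only in parents' ratings could still be presented as success on the primary outcomes.

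**Working it through.** **1. The plan's own figures.** The 134 cannot be recomputed, because the means, standard deviations and expected changes are cited but not printed. The 154 equals 134 × 1.15 = 154.1. Neither figure is disputed here. No overall false-positive rate is stated, so there is none to reproduce.

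**2. Inputs.**
- From the protocol: alpha 0.05; two primary outcomes; two informants analysed separately; three time points, hence two post-baseline changes per outcome; correlation 0.30 between outcomes; correlations 0.60 (T0–T1, T1–T2) and 0.40 (T0–T2) over time.
- Assumed: either informant counts as success; child–parent correlation r from 0 to 0.8; each multivariate interaction test has 2 outcomes × 2 changes = 4 degrees of freedom.

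**3. Number of primary tests.** One multivariate test per informant × 2 informants = 2.

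**4. Chance of at least one false rejection.** If independent: 1 − (1 − 0.05)² = 1 − 0.9025 = 0.0975. For correlated tests, simulation of two 4-df tests (1,000,000 draws), with the exact bivariate-normal result for two single-contrast tests beside it:

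| r | two 4-df tests | two z-tests |
|---|---|---|
| 0.3 | 9.6% | 9.5% |
| 0.5 | 9.2% | 9.1% |
| 0.7 | 8.5% | 8.4% |
| 0.8 | 8.0% | 7.8% |

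**5. Direction.** These are rejections in any direction. Counting only rejections whose net T2 difference favours the game, simulation with the protocol's correlations gives about 4.9% at r = 0 and 4.3% at r = 0.7, against 2.5% for a single test.

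**6. Effect of the remedies.**
- Child-report as sole primary test: error 5%, and the planning alpha of 0.05 applies unchanged.
- Alpha split, 0.025 per informant: 1 − 0.975² = 4.94% if independent. Power at 134 falls from 80% to about 71%. Keeping 80% needs about 158 completers (4-df approximation: 134 × 14.06/11.94) to 162 (1-df: 134 × 9.51/7.85).

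**7. Claims for each outcome.** A joint test over T1 and T2, followed by T2-only tests of each outcome at 0.05, does not hold 5%. Take a clear T1 effect (z = 3 on each outcome) and none at T2. The joint test then rejects in about 98% of draws, and the two T2 tests give a false result in 9.5%. The follow-up tests must address the same hypothesis as the joint test. If each outcome's own intervention-by-time interaction over T1 and T2 is tested at 0.05 after a significant joint test, the error is 4.3% with no effect anywhere and 5.0% for the null outcome when only the other one moves.

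**The case against.** The strongest reply is that no success rule is stated. If both informants had to be positive, the error would be at most 5%. Child-report planning values also suggest that the authors think of child-report as the main analysis. Both points are fair, and they make the 8–10% conditional. They do not close the gap: using child-report values for planning does not declare a primary informant, and section {20a} treats the two reports alike.

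A second reply is that a trial of improvement should count only false claims of benefit. That roughly halves the figure, to about 4.3–4.9% for r from 0.7 to 0. The comparator halves too, to 2.5%, so the near-doubling remains.

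A third is that such rules belong in a statistical analysis plan that is not shown. That holds for follow-up tests after the joint test, and the lack of them is not held against the article. It does not hold for the correction itself, because the article states where Bonferroni applies and leaves the primary tests outside it.

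Two stronger readings are tempting:
- A reader might count four primary tests (two outcomes × two informants) and quote 18.5% (1 − 0.95⁴). The plan analyses the two outcomes jointly within each informant, so the count is two.
- A reader might take 9–10% as the established risk of a false claim of improvement. The documents give neither the success rule nor the child–parent correlation, and the figure includes rejections in the harmful direction.

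**Conclusion.** The point holds in a limited form. As written, there are two primary multivariate tests, one per informant, with no ranking and no correction, and 0.05 as the only level stated. If either may carry the main conclusion, the chance of at least one false rejection is about 8–10%: 9.75% under independence, about 8% at a child–parent correlation of 0.8. This rests on the either-informant rule, the assumed correlation range and the 4-df form of the test. That 0.05 applies to each test is inferred from the planning alpha and from Bonferroni being confined to the secondary objectives.

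It should be fixed, because the choice of informant can decide the headline result. It does not undermine the design or the sample size.

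**What to change.** In section {20a}, name the child-report multivariate intervention-by-time test as the single primary test at two-sided 0.05. Move the parent-report PedsQL and SPQ into the secondary family under its Bonferroni correction.

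If a claim for each outcome is wanted, add a step after a significant joint test: test each outcome's own intervention-by-time interaction over the same time points at 0.05. Alternatively, make both the joint test and the follow-up tests T2-only. In either case report the signed T2 group difference with its 95% confidence interval.

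The cost is a few sentences, with no new data and no change to 134 or 154. A parent-report result alone could no longer carry the primary claim, and the secondary family gains two outcomes, which tightens its Bonferroni level slightly. If the investigators want both informants to stay primary, 0.025 each is the alternative, at the price in power or sample size shown in step 6. Either choice should be made before the data are analysed.

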### Interim analyses {21b}

Interim analyses are not planned beforehand. However, when after 1 year not more than half of the required sample size is met, interim analyses will be considered and executed by independent investigators. The power calculation will be executed again in order to determine if the required sample size will be doable and the study should or should not be continued.

### Methods for additional analyses (e.g., subgroup analyses) {20b}

Descriptive statistics and Pearson correlations between outcome measures are calculated. The data will be checked for outliers, which will be winsorized when found. Intervention uptake will be reported, using the percentage of the levels and worksheets that have been completed, and the part of the parent brochure that has been read. The two conditions (intervention and control group) will be compared based on baseline scores. When significant baseline differences between the conditions occur on demographics or outcome measures, and these variables are associated with the outcome measure, this will be controlled for in further analyses. Sensitivity analysis will then be executed.

When the data regarding the type of disability allows it (i.e., the group sizes are large enough), the differences in outcome measures at T0 between siblings with a brother or sister with different types of disabilities will be analyzed as well using ANOVA.

Moderation effects will be calculated using linear mixed-effect models as well, by including the moderator, and the two- and three way interaction terms with condition and time.

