### Methods in analysis to handle protocol non-adherence and any statistical methods to handle missing data {20c}

Intention-to-treat analysis will be executed. All participants that are randomized, including treatment dropouts and study dropouts will be included in the main analysis. Maximum likelihood estimation will be used for missing data. In order to determine the robustness of the results, two sensitivity analyses will be conducted: one with the data of all participants that completed all assessments and the intervention, and one with the data of all participants that completed all the assessments but not the intervention (treatment dropouts). Participants will be considered a treatment dropout when they did not complete the game. When a parent has not (fully) read the complementary information brochure, this is not considered as a treatment dropout. The latter also accounts for not making all the complementary worksheets. In addition, the number of played levels will be included as a moderator in the analyses.

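### The form of control for baseline imbalance is not fixed, and its plainest form (a covariate main effect) would leave a T0 imbalance in the analysed outcome uncorrected in the intervention-by-time estimate

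*Protocol article*

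**What the plan says.** Under Statistical methods for primary and secondary outcomes {20a}, the effect is tested in a linear mixed model in which "the main effects of intervention and time, together with the interaction effect between intervention and time, will be included in the model". The Sample size section {14} confirms that this interaction is the powered hypothesis: the calculation "is based on an interaction effect hypothesis, including between (intervention) and within (measurement point) variance". It uses correlations of 0.60 (T0–T1 and T1–T2) and 0.40 (T0–T2), so T0 is one of the repeated responses.

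Under Methods for additional analyses {20b}, the two arms are compared at baseline. The adjustment is conditional: where significant differences between them "occur on demographics or outcome measures, and these variables are associated with the outcome measure, this will be controlled for in further analyses". A sensitivity analysis follows, whose content is not described. Whether the variable enters as a main effect, with a time interaction, or as a predictor of T1 and T2 only is not stated. For moderators, the same section does give the form: "by including the moderator, and the two- and three way interaction terms with condition and time".

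Under {20c}, all randomised participants are analysed and "Maximum likelihood estimation will be used for missing data".

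**The concern.** The two instructions do not fit together well. The tested term is a difference in change from T0. A baseline variable has one value per child, so as a covariate main effect it shifts that child's three scores by the same amount and drops out of every change. An analyst who follows {20a} and {20b} in the ordinary way may therefore report an adjusted result that is the unadjusted one.

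The case that matters most is an imbalance in the analysed outcome, which {20b} covers by naming outcome measures. Its T0 score would then be a covariate in a model where it is already a response. The second trigger condition filters little here, since on the protocol's own correlations the T0 score is associated with later scores. If the intervention arm happens to start worse, regression to the mean looks like benefit; if it starts better, a real benefit is masked. An adjusted-versus-unadjusted comparison would look stable in either case.

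**Working it through.** **The plan's own figure.** The requirement of 134 cannot be reproduced, because the means, SDs and expected changes come from cited studies and are not given. The step to 154 follows from 134 × 1.15 = 154.1. Neither figure is disputed; 154 gives 77 per arm.

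**Inputs from the document.** Correlations 0.60, 0.60 and 0.40; 67 per arm analysed or 77 per arm randomised; 15% dropout ({14}). **Assumed:** outcome SD of 1 at each time, two-sided 5% baseline tests, and the covariate slopes and imbalances used in the simulations.

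**Step 1: cancellation.** Write the mean at time t as a_t + g_t·arm + b·x, with x constant within a child. Then Y_t − Y_0 has mean (a_t − a_0) + (g_t − g_0)·arm, and b·x is gone. Simulated fits, one outcome, 67 per arm, covariate imbalance 0.4 SD:

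- Complete data, unstructured covariance: T2 contrast 0.58985 (SE 0.17534) both without and with the covariate main effect.
- Complete data, compound symmetry: 0.58985 (SE 0.14954) both ways.
- Complete data, AR(1): estimate identical, but the SE moves from 0.17357 to 0.16961.
- About 19% missing at T2, unstructured: 0.62511 (SE 0.18871) becomes 0.60484 (SE 0.18828), a shift of 0.02 SD.

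**Step 2: a covariate whose effect changes over time** (slopes 0.4, 0.2 and 0.0). Complete data, unstructured: 0.396 (SE 0.174) with or without the main effect, against 0.501 (SE 0.171) once covariate-by-time is added. The main effect misses a shift of about 0.10 SD.

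**Step 3: the T0 outcome as covariate while T0 stays a response.** Under compound symmetry the T1 contrast is 0.29597 (SE 0.17374) both ways. Under an unstructured covariance the fit is degenerate: a slope of 1 on the T0 score reproduces the T0 response exactly, so its residual variance goes to zero.

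**Step 4: the bias that remains.** With equal SDs and no true effect, a T0 difference D leaves an expected difference of rho·D later. The contrast is therefore rho·D − D = −(1 − rho)D.

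- T1: −(1 − 0.60)D = −0.4D.
- T2: −(1 − 0.40)D = −0.6D.
- Significance threshold with 77 per arm: 1.96 × √(2/77) = 0.316 SD.
- At that threshold: −0.4 × 0.316 = −0.13 SD and −0.6 × 0.316 = −0.19 SD.

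Simulation agrees. In 300 data sets with D fixed at 0.32 SD and no true effect, the mean contrasts were −0.130 (T1) and −0.188 (T2), identical with T0 added as a covariate. They were −0.002 and 0.003 when T1 and T2 were regressed on arm and T0. In 20,000 null trials with 67 per arm, those with a significant positive imbalance (mean 0.40 SD) gave −0.16 and −0.23 SD, against about 0.01 SD with T0 adjustment.

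**Step 5: precision.** The variance per child behind the contrast is 2(1 − rho) for change from T0 and 1 − rho² with T0 adjustment.

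- T1: 0.80 against 0.64.
- T2: 1.20 against 0.84.

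**The case against.** The strongest reply is that the protocol nowhere says main effect only. Controlling for a variable also describes covariate-by-time or a baseline-adjusted model of T1 and T2, and both change the result. The written-out moderator terms prove little, since the three-way term is what defines moderation of an intervention-by-time effect. The form of entry is also the kind of detail a fuller document may hold. This stands as far as it goes: a reader might infer that the planned control does nothing, and the text does not support so flat a statement. What remains is that the ordinary way of carrying out {20a} and {20b} together is inert where it is most needed, and that the form could be chosen after the imbalance is seen.

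A reader might also infer that the estimate and SE never move. That is exact only for complete data, and for the SE only under some covariance structures; the plan expects dropout and uses maximum likelihood. A third tempting inference is that every imbalance stays in the primary result. It does not: a demographic with a stable effect is already removed by the change contrast. Nor is the trial biased overall, because under randomisation the contrast is unbiased on average; the figures are conditional on an imbalance that reaches significance in about 5% of trials per outcome. Stratification by sibling age balances age, but does not ensure balance on T0 outcome scores.

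Finally, moving T0 out of the response drops children with T0 data only, against the {20c} commitment to all randomised participants. That objection is sound and shapes the fix.

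**Conclusion.** The point holds in a limited form. The protocol leaves the form of baseline control open, and its plainest form does not correct a T0 imbalance in the analysed outcome or in a covariate whose effect changes over time. The size for the outcome case is −0.4D at T1 and −0.6D at T2, about −0.13 and −0.19 SD at the threshold of about 0.32 SD. For other covariates it depends on how their effect changes over time; 0.10 SD in Step 2 is illustrative.

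The result rests on the protocol's correlations, equal SDs over time, no true effect in the bias figures, and single-outcome fits. The multivariate primary model was not fitted, although the within-child cancellation does not depend on the number of outcomes. The two primary outcomes and two informants give four baseline comparisons. If each were tested at 5% and they were independent, at least one would be significant in 1 − 0.95⁴ = 19% of trials, and in fewer if they are positively correlated. The point deserves a change to the plan; it does not mean that the trial's conclusions would be wrong.

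**What to change.** Replace the clause on control in {20b} with wording such as: *Any baseline covariate enters together with its covariate-by-time interaction. The T0 score of the analysed outcome is adjusted for in all analyses, whatever the baseline comparison shows, and is never a covariate in a model in which T0 is also a response.*

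Then name one of two forms for the T0 adjustment:

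1. A longitudinal model of T0, T1 and T2 with a common T0 mean in both arms. This keeps every randomised child with a T0 score, in line with {20c}, and is the better fit to this plan. The {20a} sentence must change, because a free intervention effect at T0 is no longer in the model.
2. A model of T1 and T2 with T0 and T0-by-time as predictors. Children with T0 only then contribute nothing to the effect estimate, so {20c} would need to say so.

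The unadjusted intervention-by-time model can be kept as the sensitivity analysis, which then has something to compare. The cost is a few sentences, one or two degrees of freedom per covariate and, under the second form, the loss of T0-only children. No new data are needed, and under the protocol's correlations precision improves as in Step 5.
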